### Limitations

A potential limitation of the study is the strict exclusion criteria, which were set to eliminate the possible risk exposure of patients with pre-existing contraindications for WBV. As a result, some patients with neck pain who could have benefited from the treatments were excluded.

To minimize bias, analysts were blinded, but owing to the work setting at the trial center, the data assessor could not be blinded. To reduce potential assessor bias, very strict measurement criteria were applied.

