### Outcome Measures

#### Overview

Pre- and postintervention measurements and outcome data shall be assessed by [name]. [name] is a sport scientist with a cumulative work experience of 6 years as a physical education teacher and sports therapist. [name] is trained in using the underlisted assessment instruments and procedures.

Pain intensity, PPT, neck disability, and CJPS are measured before, immediately after, and 15 minutes after the first intervention session and after 4 weeks of the intervention. A follow-up postintervention measurement will be taken after 4 weeks.

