#### Cervical Joint Position Sense (CJPS)

The participants will wear on their head a cervical goniometer (CROM, Performance Attainment Associates) attached with a laser pointer (P2, NOBO) and will be required to sit straight and comfortably without resting their back on a chair placed 90 cm away from the target. The target is a board that can be adjusted so that the center of the board is at eye level for each participant when seated and looking straight ahead. This initial head position is defined as the neutral head position (NHP) and will be marked on the target screen. From this NHP, the blindfolded patients are instructed to rotate their head to the side and then to turn their head back to the NHP and provide a verbal signal by saying “now” when they think they have returned to the NHP with the laser pointer. The point at which they made the stop signal is marked, and the distance between this point and the NHP is measured in centimeters. This procedure will be repeated 8 times for right as well as left head rotations. A systematic review of the literature by de Vries et al [8] and colleagues demonstrated that CJPS tests are efficient in identifying CJPS acuity errors in patients with neck pain when at least 6 repetitions are performed. The CJPS test has fair to high test-retest reliability (intraclass correlation coefficient=0.39-0.78) [39] and good discriminative, convergent, and divergent validity scores [40].

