#### Pressure Pain Threshold (PPT)

The PPT will be measured using a pressure algometer (Wagner Instruments). Standing behind the seated participant, the assessor will incrementally apply pressure on the trigger point of the levator scapulae muscle at the angulus superior of the scapula until the participant calls out “now” to indicate the onset of painful pressure. The assessor stops immediately and records the reading on the algometer at which point the participant started to feel pressure pain. To enhance the reliability of the test, 3 repetitions are carried out on the left and right sides. The PPT test has high interrater and test-retest reliability (intraclass correlation coefficient=0.75-0.95) as reported in a previous study [42].

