### Randomization and Allocation of Concealment

The participants will be randomly allocated to the SRT, WBV, or BLT group. Randomization will be performed electronically using the QuickCalc software (GraphPad Software) and sealed in a brown nontransparent envelope. A physiotherapist who is not involved in the study will allocate the patients into groups. The sequencing and allocation will be concealed from the participants and other members of the research team. Furthermore, the analyst is blinded to the actual treatment of participants. All the actors involved will be unblinded after the final measurement from the last patient.

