### Ethics Approval, Study Registration, and Consent to Participate

The study will be conducted in accordance with the tenets of the Declaration of Helsinki. Ethical approval was obtained from the ethics committee of the Deutsche Hochschule für Gesundheit und Sport (DHGS-EK-2021-001), and the study was registered with the German Clinical Trials Register (DRKS00023881) and in the World Health Organization’s International Clinical Trials Registry Platform (U1111-1262-6569). Participants will be required to sign the informed consent form and return it during recruitment to the same physiotherapist who informs them of their study group allocation.

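### The randomization section states a blinding that the design lacks: participants are told their group, the single assessor is unblinded, and only the analyst is blinded

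*Protocol article*

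**What the plan says.** All references are to the protocol article.

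- **Trial Design** calls the trial single-blind and does not say who is blinded.
- **Randomization and Allocation of Concealment** states: "The sequencing and allocation will be concealed from the participants and other members of the research team". It then adds the analyst as a further blinded party and ends: "All the actors involved will be unblinded after the final measurement from the last patient".
- **Ethics Approval, Study Registration, and Consent to Participate** has participants sign the consent form and "return it during recruitment to the same physiotherapist who informs them of their study group allocation".
- **Outcome Measures, Overview** gives all measurement to one person, whose name is removed: "Pre- and postintervention measurements and outcome data shall be assessed by".
- **Limitations** says that analysts were blinded but that "owing to the work setting at the trial center, the data assessor could not be blinded". The safeguard offered is: "To reduce potential assessor bias, very strict measurement criteria were applied".
- **Pressure Pain Threshold (PPT)** has the assessor apply the pressure and wait for the participant's call. Then: "The assessor stops immediately and records the reading on the algometer at which point the participant started to feel pressure pain".
- **Cervical Joint Position Sense (CJPS)** says: "The point at which they made the stop signal is marked, and the distance between this point and the NHP is measured in centimeters".

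**The concern.** A reader of the randomization section alone would conclude that neither participants nor the person taking the measurements knows the arm until the trial is over. Two other sections say otherwise. The article thus claims a protection against bias that the trial does not have, and the claim could pass into the results paper or a later risk-of-bias assessment.

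The protection matters here because the research question is a ranking of three active treatments, and the Discussion publishes the expected order: balance training best, stochastic resonance above whole-body vibration. PPT and CJPS are the outcomes a reader would take as the more objective ones, yet both pass through the hands of someone who knows the arm. Blinding the analyst cannot remove a shift that is already in the recorded values, and averaging repeated trials reduces random error but not a systematic difference by arm.

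**Working it through.** The plan states no figure on this point, so the check is a comparison of statements.

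**1. Who knows the arm, by section**

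| Party | Randomization section | Elsewhere in the article |
|---|---|---|
| Participants | Concealed; all actors unblinded at trial end | Told their group by a physiotherapist (ethics section) |
| Assessor, as a member of the team | Concealed; all actors unblinded at trial end | Could not be blinded (Limitations) |
| Analyst | Blinded | Blinded (Limitations) |

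Only the third row agrees.

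**2. Can the first two rows be reconciled by reading concealment as pre-assignment only?** The concealment sentence alone would allow it, since it stands next to the sealed envelopes and the uninvolved physiotherapist. The closing sentence of the section does not. It puts unblinding after the last patient's last measurement and applies it to all actors. Someone who knew the arm from assignment onward cannot be unblinded at the end.

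**3. Which outcomes pass through the assessor?** There are four: pain rating, PPT, neck disability questionnaire and CJPS.
- PPT: the assessor applies the pressure, stops at the call and records the reading.
- CJPS: the passage is in the passive voice. That the assessor marks the point and measures the distance is an inference from the Overview, which names nobody else.
- The pain rating and the questionnaire are participants' own reports.

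So two of the four depend directly on the assessor.

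**4. How far does that influence reach?** In both tests the participant's verbal signal sets the endpoint, and in CJPS the participant is blindfolded. What remains open to the assessor is the application of pressure, the stopping and the reading (PPT), and the placing and measuring of the mark (CJPS).

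**5. Size.** The documents give no pressing rate, reaction time, marking error or standard deviation for either test. The size of any bias cannot be derived from them.

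**6. Work involved in masking the CJPS distances.** There are 8 repetitions to each side, so 8 × 2 = 16 trials per occasion. There are 5 occasions, so 16 × 5 = 80 distances per participant. As of May 2022, 20 were enrolled, which leaves 45 − 20 = 25 to come, or 31 if the 2 extra participants per group are recruited (45 + 6 − 20). That is 25 × 80 = 2,000 to 31 × 80 = 2,480 distances, plus any outstanding visits of the first 20. All of them have to be measured by someone under the present plan as well.

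**The case against.** The strongest reply is that the authors disclose the problem. The Limitations section says that the assessor is unblinded, gives the reason, names the bias and offers a safeguard. This stands: a reader might infer that the lack of assessor blinding is hidden, and it is not. Disclosure in one section does not, however, correct the opposite statement in another.

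Second, concealing the sequence before assignment and blinding the assessor afterwards are different things. This also stands. Nothing here suggests that allocation could be foreseen, and the randomization itself is not in question. The conflict rests on the sentence about unblinding at the end.

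Third, a reader might infer that the single-blind label is wrong. It is not shown to be: it fits a trial in which only the analyst is blinded. It merely fails to name that party.

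Fourth, the article fixes no pressing rate and does not describe the strict measurement criteria. In a condensed article such detail may sit in the full protocol, so its absence is no finding.

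Fifth, the participant's signal limits the assessor's control. This is right, and it is why the point says only that knowledge of arm can influence the readings.

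**Conclusion.** The blinding statements contradict each other and must be reconciled. Participants and the only assessor know the arm; the analyst alone does not. Two of the four outcomes, PPT and CJPS, are therefore open to assessor expectation, in part and to an unknown extent.

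A reader might go further and infer that the PPT and CJPS results will be biased toward the published ranking, or attach a number to the shift. The documents support neither. They show a route for bias, not its presence or its size, and any figure would come from invented inputs.

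The conclusion rests on two readings: that the statement about unblinding all actors includes participants and assessor, as its wording says, and that the person named in the Overview also marks and measures CJPS, since no one else is named.

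**What to change.** **1. Reconcile the text.** In the randomization section, limit concealment to the period before assignment and replace the closing sentence on unblinding. State that participants and the assessor are not blinded after assignment and that the analyst is. In Trial Design, specify that single-blind refers to the analyst. This costs nothing beyond a less favourable blinding statement.

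**2. Mask the CJPS distance measurement for the assessments still to come.** Mark the neutral head position and the stop points on a separate sheet for each occasion, labelled with a code that hides arm and occasion. Let the blinded analyst measure the distances. Record the date of the change, so that values obtained in the two ways can be told apart.

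The second step needs paper sheets, a code list kept from the analyst, and the analyst's time for the 2,000 or more distances counted above; no extra staff and no change for participants. It has limits. The placing of the mark stays unblinded. Participants already measured were measured the old way, and those in mid-course will have both. If the team regards the change as major, its own amendment section requires notice to the ethics committee and the registry.

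No change to the PPT technique is proposed: altering it after 20 of 45 participants were enrolled would mix two methods of applying the test.

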### Dissemination Policy

The results will be communicated to the participants and shared publicly through publication in peer-reviewed journals and at international scientific conferences.

### Conclusions

The outcome of this study will particularly elucidate the effects of SRT, WBV, and BLT on pain and function in patients with chronic neck pain.

## Abbreviations

BLT: balance training
CJPS: cervical joint position sense
GABAergic: γ-aminobutyric acid–mediated
NHP: neutral head position
NPAD-d: German version of the Neck Pain and Disability Scale
NRS: numeric rating scale
PPT: pressure pain threshold
SRT: stochastic resonance therapy
WBV: whole-body vibration
